## Methods

### Study Design

The *InvolveMENT* project uses a participatory, multidisciplinary, multiphase, mixed methods research design [26] to adapt digital mental health services to meet the mental health needs of national minority, Indigenous, and refugee youth in Norway. The four stages of the research include a cohort study (work packages [WP1]) to assess the needs, barriers, and facilitators of service use; qualitative studies (WP2) to explore the perspectives of youth from these groups on digital mental health services; co-design activities (WP3) to develop recommendations for adapting digital services; and an evaluation study (WP4) to assess the adapted digital mental health services through a randomized controlled trial (RCT) and a qualitative study.

The project will use the Trials within Cohorts (TwiCs) design to test the acceptability, effectiveness, cost-effectiveness, and safety of the adapted digital services in WP4. This design offers several advantages over conventional RCTs and quasi-experimental approaches, particularly in studies involving hard-to-reach populations. TwiCs design enables fast and efficient recruitment to the RCT, as participants are already enrolled in the broader cohort from which trial participants are selected. It helps to reduce attrition rates because individuals in the control group are not informed about interventions they are not offered, thereby minimizing disappointment bias. Moreover, by avoiding disclosure of unavailable treatments, the design enhances the generalizability of results, as participants’ expectations and behaviors are less likely to be influenced by knowledge of the intervention [27]. One-year rolling recruitment is used to compensate for natural attrition.

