#### Randomization

In WP4, participants who meet the inclusion criteria will be randomly allocated in a 1:1 ratio using Microsoft Excel, either to receive the intervention (the adapted digital services) or to continue with usual care as part of the control group. Those assigned to the control group will not be informed that they are part of a trial or that other participants are receiving an intervention. This approach is consistent with the TwiCs design [27,33], which stages and tailors the consent process to reflect real-world clinical practice. The design ensures that individuals receiving usual care are not informed about treatments they will not be offered, thereby minimizing potential for disappointment bias.

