#### Measurement Tools

Measurement tools in the cohort study (WP1) and the RCT (WP4) include self-report questionnaires, PHQ-9, the Generalized Anxiety Disorder scale [30], the Flourishing Scale [31], the Children’s Somatic Symptoms Inventory 8 [32], and single variables to determine participants’ familiarity with, use of, and satisfaction with digital services, as well as their perspectives on service providers’ cultural and linguistic competence and youths’ preferences regarding continuity and confidentiality in care.

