#### Data Analysis

Quantitative data analyses will be carried out for WP1 and WP4. In WP1, data analysis will include univariate analyses for descriptive statistics, whereas factors associated with service use will be assessed using correlation analyses, regression models, and multiple regression models to explore multiple predictors and adjust for confounders, for example, generalized linear models and linear and generalized additive models for nonlinear associations between predictor and outcome. Temporal changes will be assessed using mixed models to assess factors affecting service use.

To assess the use and acceptability of the intervention, that is, the adapted digital mental health services for youth, we will use data from the RCT to determine the proportion of participants who report using it. An intention-to-treat analysis will be used to test the effectiveness of the intervention offer, whereas an instrumental variables analysis will be applied to determine the effectiveness of the received intervention [48]. The primary outcome will be the PHQ-9 at 12 months of the trial. Subgroup analyses will be carried out for different minority groups. Results will provide data on variability in depression outcomes in the different groups. Safety will be assessed by determining the proportion of participants with deteriorated mental health status through higher PHQ-9 scores. Service satisfaction will be assessed using single-item questions, each targeting participants’ satisfaction with 1 of 8 different types of digital services. A cost-effectiveness analysis of the intervention for youth will be carried out by undertaking a cost-consequences analysis [49]. It will compare individuals taking advantage of the adapted services with those who do not. The analysis will take a societal perspective, relating costs associated with introducing the new interventions and attributable to youths’ mental health, school absence, and work productivity (if they are in work), as well as their quality of life.

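### The cost-consequences analysis is worded as users against non-users of the adapted services, not as a comparison of the randomised arms

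*Protocol article*

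**What the plan says.** All references are to the protocol article.

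- **Study Design** says that the project will use the Trials within Cohorts "design to test the acceptability, effectiveness, cost-effectiveness, and safety of the adapted digital services in WP4".
- **Randomization** describes the allocation of eligible youth: "randomly allocated in a 1:1 ratio using Microsoft Excel, either to receive the intervention (the adapted digital services) or to continue with usual care".
- **Data Analysis**, on effectiveness: "An intention-to-treat analysis will be used to test the effectiveness of the intervention offer", and "an instrumental variables analysis will be applied to determine the effectiveness of the received intervention".
- **Data Analysis**, on uptake: "we will use data from the RCT to determine the proportion of participants who report using it". Study Outcomes treats that same proportion as the measure of acceptability.
- **Data Analysis**, on economics: "A cost-effectiveness analysis of the intervention for youth will be carried out by undertaking a cost-consequences analysis". The next sentence sets the groups: "It will compare individuals taking advantage of the adapted services with those who do not". The perspective is societal. It covers the cost of introducing the services and items tied to mental health, school absence, work productivity and quality of life.

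No arm-based comparison, instrument or covariate adjustment is stated for the economic analysis. The confounder adjustment mentioned earlier in Data Analysis belongs to the cohort models of service use (WP1).

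**The concern.** Youth decide after allocation whether to use the services. The article itself names language, trust, and fear or shame as influences on service use (the Introduction's sections on service use and digital services; Anticipated Findings). The same factors plausibly affect school attendance, work, care costs and quality of life. A contrast by use is therefore observational, even though it sits inside a randomised trial.

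Cost-effectiveness is one component of objective 5, and the project's recommendations go to service providers who decide on implementation. If the sentence is followed, the economic result will rest on self-selected groups, and it will answer a different question from the intention-to-treat result on the PHQ-9 reported beside it.

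**Working it through.** **1. The contrasts side by side (Data Analysis).**

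| Question | Groups or method stated | Protected by randomisation? |
|---|---|---|
| Effect of the offer | Intention to treat | Yes |
| Effect of receipt | Instrumental variables | Yes, under the usual instrument assumptions |
| Costs and consequences | Users against non-users | No |

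The plan separates offer from receipt for effectiveness and uses the allocation for both. Only the economic contrast does without it.

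**2. How large could self-selection be?** The plan has no figure to reproduce here, so this is an illustration.

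From the article: 300 randomised 1:1 with 20% dropout gives 300 × 0.8 = 240 evaluable, 120 per arm. The planned effect, d = 0.35, serves only as a yardstick.

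Assumed, because the article gives no value:
- uptake u = 50% in the offered arm and no use among controls, giving 60 users, 60 offered non-users and 120 controls;
- a standardised prognostic factor Z correlated 0.5 with an outcome of SD 1;
- a logistic model for use, with odds ratio (OR) 1.5, 2 or 3 per SD of Z;
- a true effect of zero.

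Let m be the mean of Z among users. At 50% uptake, m = 2 × E[Z / (1 + exp(−Z ln OR))]. Offered non-users then have mean −m and controls 0.

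- All others: (60 × (−m) + 120 × 0) / 180 = −m/3.
- Users minus all others, on the outcome: 0.5 × (m + m/3) = 2m/3.
- Users minus offered non-users, on the outcome: 0.5 × 2m = m.
- Users minus controls, on the outcome: 0.5 × m.
- Offered arm minus control arm: 0.5 × [(60m − 60m)/120 − 0] = 0.

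Numerical integration for m gives these spurious differences, in SD:

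| OR per SD | m | Users vs all others | Users vs offered non-users | Users vs controls | Randomised arms |
|---|---|---|---|---|---|
| 1.5 | 0.195 | 0.13 | 0.20 | 0.10 | 0 |
| 2 | 0.313 | 0.21 | 0.31 | 0.16 | 0 |
| 3 | 0.441 | 0.29 | 0.44 | 0.22 | 0 |

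**3. Sensitivity to uptake.** For users against all others, letting uptake run over 30%, 50% and 70% with the same three odds ratios gives a range of 0.09 SD (70%, OR 1.5) to 0.37 SD (30%, OR 3).

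**4. Cross-check without the logistic model.** If users and non-users in the offered arm differ by s SD on the outcome, users against all others differ by s(1 − u)[1 + u/(2 − u)]. At u = 0.5 and s = 0.35 this is 0.35 × 0.5 × (1 + 0.5/1.5) = 0.23 SD, in line with the table.

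**The case against.** **The wording may be loose for the arms.** Study Design ties cost-effectiveness to the randomised design, so the authors may have meant offered against usual care. This is possible but strained: use is measured separately, as an acceptability outcome, and the same paragraph distinguishes offer from receipt. If the arms were meant, the sentence still needs changing.

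**An analysis plan or health-economic plan that is not shown may add adjustment or an instrument.** It may, so one should not assume that the comparison will be unadjusted. The article nevertheless fixes the groups, and adjustment would rely on measured confounders where the arm comparison needs none.

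**The comparator is not defined.** This stands. The article does not say whether the non-users are offered youth who decline, controls, or both, so a reader should not infer that controls and decliners will be pooled. The table shows each reading; all three are biased when use is self-selected.

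**Controls may use the services.** This also stands. Study Population and the data collection section expect exposure outside the trial, and the existing services sit on a public channel. Such use would change the illustrative group sizes and dilute the arm comparison. It does not make a user comparison unconfounded.

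**Stronger readings that the documents do not support.**
- That every cost and consequence is confounded: the cost of introducing the services does not depend on who chooses to use them.
- That the analysis would have an inflated false-positive rate: no hypothesis test or threshold is stated for it, and the 0.05 level belongs to the trial's sample size.
- That the surveys lack the items needed: "Measurement tools in the cohort study (WP1) and the RCT (WP4) include self-report questionnaires, PHQ-9, the Generalized Anxiety Disorder scale" opens a list that is not said to be complete, and an article may leave such items to the full protocol.

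**Conclusion.** Wrong as written. The economic comparison is defined by use after randomisation, which conflicts with the article's statement that the randomised design tests cost-effectiveness and with its own handling of effectiveness. This is a stated choice of groups, not detail left out of an article.

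The size and direction of the bias are unknown. Under the declared assumptions it is about 0.13 to 0.29 SD for users against all others, which is 37% to 83% of the planned d (0.13/0.35 and 0.29/0.35). Uptake, odds ratios, the correlation of 0.5 and the absence of use among controls are all assumptions, so the range shows only that the bias need not be negligible. The primary outcome, the intention-to-treat and instrumental-variables analyses of the PHQ-9, and the sample size are not affected.

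**What to change.** Replace the sentence in Data Analysis that sets the economic comparison groups with:

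*The cost-consequences analysis will compare the two randomised arms (intention to treat); an analysis by receipt will use the randomised offer as instrument, as for PHQ-9, and is supplementary; any user versus non-user comparison is descriptive only.*

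This costs one sentence, with no extra participants and no change to the sample size. The downside is that the main economic estimate then refers to the offer. It is diluted by non-use in the offered arm and by any use among controls, as the intention-to-treat effectiveness estimate already is. Recording use of the adapted services in both arms would let the supplementary analysis take account of both.

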### Ethical Considerations

According to the World Medical Association’s Declaration of Helsinki, vulnerable groups may participate in research when it is responsive to their health needs and priorities and when appropriate protections are in place. This project is supported by strong legal and ethical arguments, particularly because the voices of youth from minority backgrounds are seldom heard and they remain underrepresented in health research, despite existing public policies and legislation advocating for inclusion.

Participants are aged ≥16 years, granting them the legal right to independently decide on their participation. To ensure informed consent, participants receive both written and verbal information. Safeguarding procedures have been developed in collaboration with youth minority representatives and professionals working with these groups. These procedures include mechanisms for recommending additional health care support when needed, thereby protecting the well-being and integrity of participants.

While the researchers maintain overall responsibility for the project, it is designed as a collaborative effort involving multiple stakeholder groups. These include youth representatives from minority backgrounds, health care professionals, and service providers. Their involvement spans all phases of the project, from planning and design to data analysis and dissemination, to ensure cultural sensitivity and relevance. This includes co-development of research materials, such as information sheets, consent forms, interview guides, survey instruments, and promotional content. Such collaboration helps minimize the risk of misrepresentation or harm to minority youth participants. Stakeholders also contribute perspectives during data analysis and are invited to co-author scientific and popular publications, as well as participate in media and social media outreach. Written and signed collaboration agreements have been established to clarify the rights and responsibilities of all parties involved.

The project uses the TwiCs design, which asks potential participants to consent to the use of their identifiable data, to be recontacted, and to allow their data to be used in evaluating interventions [27]. Only those offered an experimental intervention are informed about the developed intervention, aligning the consent process more closely with real-world clinical practice. This approach is considered more ethical than traditional models that require full disclosure of all potential interventions upfront [33,50]. TwiCs studies have received ethical approval in 10 countries [33], including youth mental health research [51]. Youth participants were offered gift cards for their involvement in each activity, in appreciation of their time and contributions: NOK 100 (US $10) for surveys (WP1/WP4), NOK 250 (US $25) for qualitative interviews (WP2), and NOK 600 (US $59) for workshops (WP3).

The University of Stavanger, through SHARE—Centre for Resilience in Healthcare, holds overall responsibility for data management, with the project lead serving as data steward. The project adheres to General Data Protection Regulation (GDPR) [52] and Norwegian ethical standards [53], ensuring informed consent and secure handling of personal and sensitive data. Consent procedures include options for recontact and data sharing, with safeguards for anonymity and participant rights. All data handling, including classification, storage, and processing, follows strict protocols to ensure privacy, integrity, and ethical compliance throughout the project lifecycle. Sensitive data are stored on a Sensitive Data Services server.

Ethical approval for this project has been granted by the Regional Committees for Medical and Health Research Ethics (ID 780840). Additionally, collective consent for Sámi youth participants has been approved by the Expert Ethics Committee for Sámi Health Research (ID 1133459). Moreover, Sikt, the Norwegian Agency for Shared Services in Education and Research, has considered the processing of personal data to be lawful based on consent (GDPR Article 6(1)(a)) and explicit consent (GDPR Article 9(2)(a), applicable to special categories of data) [52] (reference number 374832).

## Results

We have completed recruitment to the project of youth representatives from all national minority, Indigenous, and refugee youth groups, which are the end users of the research. The panel now consists of 32 youth representatives. Ethics approval has been granted. A recruitment plan has been developed, and recruitment is estimated to start in December 2024. Draft versions of the cohort survey have been piloted in English, Norwegian, Arabic, and Dari, with a separate sample of 1500 participants [41]. This pilot study was conducted before the main data collection and included youth from both the majority population in Norway and those with immigrant and refugee backgrounds. On the basis of feedback from the pilot, the survey was subsequently adapted in collaboration with youth minority representatives and other project partners. This cohort study has been translated into 14 languages and will include up to 1500 youth who identify as belonging to national minority, Indigenous, or refugee backgrounds. In addition, another 1500 youth who do not belong to these groups will be included to enable meaningful comparisons between minority and nonminority populations. Youth minority representatives have also contributed input to the planning of qualitative studies. Funding was obtained from the Research Council of Norway for the time period from July 1, 2023, to June 30, 2027. Data collection started in January 2025, after submission of the manuscript (November 18, 2024).

## Discussion

### Anticipated Findings

The *InvolveMENT* project will offer an understanding of the mental health status of youth with national minority, Indigenous, and refugee backgrounds, together with their familiarity with and use of digital mental health services. This will supplement the existing research evidence, which only to a limited extent reports on perceptions of the impact of digital services on mental health among groups of minority youth [54]. While existing platforms provide general access to support, they often fall short in addressing the culturally specific requirements of these populations. Together with language needs, this can undermine youths’ trust in service providers and ultimately serve as a barrier to the use of services [24].

Adapting digital mental health services also holds the potential to address challenges resulting from refugee youths’ limited knowledge about the national health system and to reduce the harmful effects of mental illness–related stigma [55]. Through both survey data and qualitative interviews, the project will explore how youth from diverse backgrounds understand mental health, their experiences with digital services, and their preferences for culturally relevant support. These insights will inform the co-design process involving minority youth and professionals working closely with them, resulting in concrete proposals for culturally adapted, equitable, and sustainable digital mental health services.

The final phase will bring new knowledge about the acceptability, effectiveness, cost-effectiveness, and safety of digital services aimed at meeting the needs of minority ethnic youth in Norway. Others have stressed the importance of integrating user experiences to assess acceptability, self-reported effectiveness, and satisfaction with services [24]. This phase will lay the groundwork for future trials by identifying variability in mental health and service needs across different groups.

An expected impact of the project is to increase the proportion of minority youth who seek and receive appropriate digital support at an early stage, thereby contributing to timely diagnosis, intervention, and prevention of prolonged mental health complaints. As found by others, digital mental health interventions have the potential to support youth with refugee backgrounds who may be reluctant to consult mental health professionals due to fear or shame [24].

Moreover, by establishing a cohort using the TwiCs design, the project also creates opportunities for testing additional interventions during and beyond the 4-year study period. The project will also expand international research networks and explore the development of future collaborative studies focused on minority youth in diverse global contexts.

### The Involvement of Youth Throughout the Research

The *InvolveMENT* project marks the first time national minority, Indigenous, and refugee youth—whose voices have rarely been heard—are actively involved in assessing and developing digital mental health services. Research using participatory approaches, which actively engage youth and integrate cultural elements into interventions, has been found to facilitate the development of programs that meet the needs of minority youth, such as those from Indigenous backgrounds [56]. It is our hope that the extensive involvement of youth in the project may also contribute to reducing concerns about privacy and confidentiality, which are common among these groups of youth [57]. Together with the involvement of professionals providing services for these groups of youth, the extensive and active involvement of youth in co-design processes ensures that their needs remain at the center of the research aimed at the development of adapted, equitable, and sustainable health care support services.

### Strengths and Limitations

The strengths of the *InvolveMENT* project include the novelty of the project, which aims to improve mental health outcomes for national minority, Indigenous, and refugee youth in Norway by addressing the lack of culturally sensitive digital services tailored to their needs. The broad range of methodologies used will contribute to a better understanding of youth from minority ethnic groups, in particular with regard to the development of culturally adapted services that are suited to meet their mental health needs. A key strength lies in the youth-centered approach, ensuring that services are equitable, relevant, and sustainable, and marking the first time these populations are directly engaged in shaping mental health support in Norway. The main risk of this project is the recruitment of national minority, Indigenous, and refugee youth for the cohort (at least 1500 youth) and for the qualitative study. There are no exact population figures for the included minority groups, but estimates suggest 50,000 to 65,000 (age group 16‐25), and recruitment will take place through multiple channels. A recruitment rate of 2% to 3% is a conservative estimate as participation rates in youth surveys were 73% to 87% in the Norwegian *Ungdata* survey [58] and 77% in our pilot [42]; and minority youth will be informed that the project aims to hear their views and that they will influence service development, which will encourage participation. The substantial involvement of youth representatives and coresearchers from minority groups in the project will be a great advantage for the recruitment process. Another limitation is the reliance on self-reported measures, which may introduce bias due to cultural differences in language and response styles. This concern may be particularly relevant in culturally diverse populations, where language, response styles, and social desirability norms can influence how questions are understood and answered [59]. However, the randomized design enhances internal validity, and the integration of qualitative interviews with survey data allows for triangulation that may help mitigate these limitations. By assessing the acceptability, effectiveness, cost-effectiveness, and safety of adapted services, the project not only enhances early intervention and reduces long-term mental health issues but also lays the foundation for future trials and international collaboration. Its findings will generate vital knowledge, expand research networks, and offer scalable models for culturally adapted digital mental health services worldwide.
